### Interventions

#### Breaking free online health and justice

BFO is an online treatment program for substance-involved offenders. Clinical content of BFO has been informed by the available evidence-base around effective biopsychosocial and behavioral intervention approaches for addressing drug and alcohol misuse (National Treatment Agency for Substance Misuse 2006a, b; NICE 2007, 2011, 2012), including cognitive-behavioral principles (Beck 1993; Beck et al. 2011), and other approaches including mindfulness-based relapse prevention (Marlatt et al. 2010; Marlatt and Donovan 2005).

When an individual first uses BFO, they complete a psychometric assessment developed by the authors, the ‘Recovery Progression Measure’ (RPM: Elison et al. 2016a; 2017b, which is contained within the program. The RPM measures baseline levels of functioning, and treatment-related changes in functioning, across six domains; ‘negative thoughts’, ‘emotional impact’, ‘unhelpful behaviors’, ‘difficult situations’, ‘physical sensations’, and ‘lifestyle’. Data generated via completion of the RPM is then utilized by the BFO program to populate a visual depiction of a six-domain biopsychosocial model, the ‘Lifestyle Balance Model’ (LBM: Davies et al. 2015). The LBM forms the theoretical underpinnings of the program and is based on the five-factor model used in cognitive behavioral therapy (Greenberger and Padesky 1995; Williams and Chellingsworth 2010). The LBM (see Fig. 1) acts as a clinical formulation to help the user understand the domains of their functioning that may be implicated in their substance misuse.

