### Procedure

Site investigators from the research team will work with the support of members of the team of substance misuse practitioners working in the prison to inform potential participants of the study. Site investigators will be responsible for completing screening, consent and randomization. Site investigators and practitioners will be responsible for conducting baseline and 4-week post-baseline assessments. Practitioners will be responsible for delivering both BFO and the standard treatments received by the two study groups. Site investigators will be responsible for conducting 3- and 6-month follow-up assessments. All site investigators and practitioners have been vetted and security cleared to work in prisons by HMPPS and have enhanced clearance via the UK Government Disclosure Barring Service. The site investigators have trained all participating practitioners in delivering BFO as CAT and have also conducted training around RCT methodology. All practitioners are trained and experienced facilitators of structured substance misuse interventions. Both site investigators and practitioners have received training in ethics and confidentiality issues when working with offenders in secure settings.

All prospective participants that potentially meet the study criteria will be informed of the study’s objectives and requirements using the Participant Information Sheet and Informed Consent Form before any screening procedures are performed. If willing to participate in the study, participants will be requested to provide written consent after being given sufficient time to consider their participation and having had the opportunity to ask for further details. During the informed consent procedure, participants will be provided with information about the fact they can withdrawal from the study at any time without giving a reason, and without their withdrawal affecting their recovery and rehabilitation support. Additionally, they will be assured that when their data are collected, no identifiable information can be traced back to them, and that their data will be fully anonymized.

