The Informed Consent Form will be signed and dated by both the participant and the site investigator, and the participant’s preferred mode of contact (e.g. telephone, email etc.) and contact details for the completion of follow-up assessments will also be noted at this point. The participant will be provided with a copy of the signed consent form and the Participant Information Sheet. The original consent forms will be retained in a secure storage facility separately from source data to protect against breach of privacy and participant anonymity.

If written consent is given, each participant will then be screened for eligibility by the site investigator before then being randomized to either the BFO or control group. Randomization will occur at the level of the individual participants, with participants being assigned to one of the study groups following the generation of a random allocation sequence via the *Research Randomizer* (from the Social Psychology Network- Urbaniak and Plous 2011). Sequentially-numbered opaque sealed envelopes containing the treatment group that the participant will be allocated to will be delivered to the research site prior to commencement of the study. The participant number will be determined according to the order of enrolment in the study. The site investigator will assign and open one sealed envelope per participant. A screening log, including the participant number and treatment group assigned by randomization and any subsequent reason/s for exclusion from the study (if applicable), will then be completed by the site investigator.

No longer than 2-weeks after being randomized and completing the eligibility screening, both study groups will complete a battery of assessments to collect data around primary and secondary outcomes and demographic information including age and ethnicity. This battery of assessment will be delivered digitally via desktop computers within the prison IT suites. The assessment for the BFO group will be completed within the BFO program. The control group will complete the measures via a specially developed digital assessment platform which will deliver the same assessment that is included in the BFO program, but without providing access to any of the digital intervention content provided by BFO.

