Specialist statistical support has been sought from colleagues at one of the collaborating academic institutions (University of Manchester), who have provided advice during protocol development and will provide ongoing advice throughout the study. When analyzing differences between the two study groups at each of the outcomes data time-points, (4-weeks post-treatment, 3- and 6-month follow-ups) baseline scores will be controlled for as post-treatment between-group differences may reflect both treatment effects and also group differences at baseline that randomization may not have addressed. Differences between the groups in post-treatment scores will be ascertained using estimated marginal means.

Effect sizes will also be calculated to examine robustness of between-group differences and within-group changes over time, using partial eta squared (ὴ^2^), which is an appropriate measure of effect size for ANCOVA. The numbers of participants fulfilling clinical threshold scores for substance dependence, depression and anxiety at baseline and post-treatment will also be examined.

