Potential limitations of the methodology include the fact that it will be difficult for the investigators or the practitioners working in the prison substance misuse service to be blinded to the allocation of participants to each of the two study groups. This is because the investigators will have to randomize participants and then organize the BFO groups in the prison, and so they will need to know which group each participant is randomized to in order to do this. Although the practitioners will not immediately know which group each participant has been allocated to, very shortly after randomization they will receive a list of all participants in the BFO group. This is because they will need to check attendance to the group, which is particularly important in a secure prison environment in which the whereabouts of individual offenders must be accounted for at all times. It is also a requirement of prison regimes in the UK for any member of staff facilitating a group session to know ahead of the session which offenders will be attending. This is so staff can be aware ahead of the session of any special circumstances surrounding each offender that may need to be taken into account or may pose a risk for any reason, for example if a specific offender had recently had any emotional or behavioral difficulties etc.

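### Baseline scores used for adjustment are collected after randomization, and on different platforms in the two arms, so they are not guaranteed to be independent of allocation

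*Protocol article*

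**What the plan says.** All references are to the protocol article.

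- **Order of events (Procedure).** After consent, "each participant will then be screened for eligibility by the site investigator before then being randomized to either the BFO or control group". The battery covering the primary and secondary outcomes comes after that: "No longer than 2-weeks after being randomized and completing the eligibility screening, both study groups will complete a battery of assessments".
- **Platform (Procedure).** For one arm, "The assessment for the BFO group will be completed within the BFO program". For the other, "The control group will complete the measures via a specially developed digital assessment platform", which carries the same items without intervention content. The same section says that entering BFO needs an access code from a practitioner, a personal account and acceptance of the program's terms.
- **Staff (Procedure and Discussion).** "Site investigators and practitioners will be responsible for conducting baseline and 4-week post-baseline assessments". Investigators know the allocation because they randomize and organize the BFO groups. Of the practitioners, the Discussion says "very shortly after randomization they will receive a list of all participants in the BFO group".
- **Use of the scores (Data analysis).** At 4 weeks, 3 months and 6 months, "baseline scores will be controlled for as post-treatment between-group differences may reflect both treatment effects and also group differences at baseline".
- **Nature of the outcome (Measures).** The primary outcome is self-reported substance use, built from two questions.

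**The concern.** Covariate adjustment in a randomized trial is safe because a covariate measured before allocation cannot be affected by allocation. The Data analysis section relies on this when it treats baseline differences as something randomization failed to balance. With the sequence as written, a baseline difference could be chance imbalance or could have been caused by allocation, and the model cannot tell the two apart. It would remove both, and the second kind would enter the treatment estimate.

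The primary outcome and its baseline are self-reports, so there is no objective measure to offset changed reporting. Every baseline-adjusted comparison is exposed, primary and secondary. The limitations in the Discussion acknowledge lack of blinding but do not mention the timing of baseline.

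A smaller consequence is that men who leave between randomization and the battery have no observed baseline, although the analysis population is everyone randomized.

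**Working it through.** No figure in the article bears on this point, so there is nothing to reproduce. The check has two parts.

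**1. Can baseline depend on allocation?**

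- The sequence is consent, eligibility, envelope, then battery, with a gap of up to 2 weeks after the envelope.
- The BFO arm answers inside BFO, and entry to BFO needs a code and an account. It follows that a BFO man has logged in to the program, and so can know his arm, before he answers.
- Controls answer the same items on another platform. Arm and platform are therefore fully confounded at baseline.
- Site investigators know the allocation at once and practitioners soon after. The battery is delivered digitally and no staff rating is described, so this route is secondary.

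Nothing elsewhere in the article provides a pre-allocation measurement of the outcomes. The Measures section mentions substance use before the current sentence but does not say when it is recorded.

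**2. What would a shift do?**

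Let *b* be the within-arm slope of follow-up on baseline. Let *s* be the shift in measured baseline in the BFO arm caused by allocation, in SD. Let *k* be the fraction of that shift still present at follow-up. For a linear ANCOVA,

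bias in adjusted difference = k·s − b·s = (k − b)·s.

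The article gives none of the three values, so all are assumptions. With b = 0.6:

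| Scenario | s = 0.1 SD | s = 0.2 SD |
|---|---|---|
| Baseline only (k = 0) | −0.6 × 0.1 = −0.06 | −0.6 × 0.2 = −0.12 |
| Fully persistent (k = 1) | 0.4 × 0.1 = +0.04 | 0.4 × 0.2 = +0.08 |

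The outcome is scored so that higher means more use, so a negative bias favors BFO. If BFO men report less at baseline (s negative), every sign reverses.

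A simulation of the baseline-only case used 60 per arm, no true effect, and 4,000 runs per setting. With outcomes in SD units, the baseline–outcome correlation is the slope.

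| Correlation | Shift (SD) | Mean bias (SD) | Rejection at nominal 5% |
|---|---|---|---|
| 0.3 | 0.1 | −0.024 | 5.5% |
| 0.5 | 0.2 | −0.101 | 9.3% |
| 0.7 | 0.3 | −0.211 | 35.0% |

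The results follow −b·s closely. They run from almost no consequence to a serious one, depending entirely on the assumed inputs.

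**The case against.** The strongest reply is that the text shows baseline could be affected, not that it will be. The items are the same in both arms, the battery precedes the 4-week treatment, and the article does not say when participants are told their arm. That is fair, and it is why no size can be claimed. It does not restore the independence that adjustment presumes.

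A second reply is that adjustment may help. If a reporting shift persists fully, the bias with the post-randomization baseline is 0.4·s at a slope of 0.6, against the full s with a clean baseline. This also stands: the direction is unknown, and moving baseline does not cure biased reporting at follow-up. But relying on two reporting errors to cancel is not a reason to keep the order.

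A reader might also infer stronger points that the documents do not support:

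- **That BFO's feedback contaminates the RPM baseline.** The Interventions section says "Data generated via completion of the RPM is then utilized by the BFO program to populate a visual depiction". Feedback built from the RPM answers comes after them and cannot change them. It could affect other items only if they follow the display, and no item order is given.
- **That unblinded staff are the main source of bias.** The battery is digital self-report, and the lack of blinding is already acknowledged.
- **That loss before baseline cannot be repaired, or contradicts the all-randomized analysis.** A missing baseline can be imputed or modelled jointly with the outcomes, and the statistical analysis plan that may say so is not shown.
- **That the bias is a known share of the detectable difference.** The article states no effect size, and the slope and shift are assumed. The linear formula also does not carry over directly to the Poisson-type model that the Data analysis section expects.

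**Conclusion.** The concern holds as a design weakness. The covariate in the outcome comparisons is measured after allocation, by self-report, with arm and platform confounded, and so is not guaranteed to be independent of treatment. The main routes are participants' knowledge of their arm and the different platforms; staff knowledge is secondary.

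Any allocation-induced shift would generally bias the adjusted effect. The linear formula gives zero only where the persisting fraction happens to equal the slope. The magnitude is illustrative: 0.06 to 0.12 SD if the shift affects baseline only, with an assumed slope of 0.6 and shift of 0.1 to 0.2 SD, and smaller with the opposite sign if it persists fully. Neither size nor direction can be derived from the document.

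The missing baselines of men lost before the battery are a secondary matter that analysis can handle. A true pre-allocation baseline cannot be recovered afterwards, so the order of events is the part to change.

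**What to change.** Change the order to consent, eligibility, baseline battery, then opening of the envelope. Use the existing stand-alone assessment platform for both arms at baseline. Keep the RPM that BFO presents at first log-in as part of treatment only, not as trial data.

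If batching is wanted to keep the interval from baseline to treatment short, batch the battery together with the envelope opening. Batching the envelopes alone would leave men who were assessed early waiting longer.

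The cost is modest: a reordered visit and revised wording, on a platform that is already planned. Some men will complete a baseline and not be randomized, and BFO men will answer the RPM once more.

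If reordering is no longer possible, state the post-randomization baseline as a limitation. Add a sensitivity analysis without that covariate, or one adjusted only for information recorded before allocation. Substance use before the current sentence would qualify only if it was itself recorded before the envelope was opened.

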### Standard treatment

Both study groups will receive standard treatment as part of the study design. It is expected that there will be a degree of heterogeneity within both the BFO and control groups in terms of the ‘standard treatment’ each participant receives. Information regarding the specific standard treatments each participant receives will be collected, including the specific standard treatments each participant receives, the number of sessions completed, what kind of practitioner has delivered it, and also the medications each participant may have been prescribed during the course of the study (see Additional file 1: Appendix B). These data will allow comparisons to be made between different control treatments.

In terms of the psychosocial and behavioral support available in the participating prison, low-intensity group-based interventions are usually delivered by key-workers in alcohol and drug misuse services and include techniques such as motivational interviewing and contingency management. These group-based interventions will be delivered with groups of participants that are of a similar size to the group sessions of BFO, i.e. groups of 10 participants. In order to avoid violation of the stable unit treatment value assumption, participants in the BFO group will receive their group-based standard treatment in groups that are run separately from the group-based standard treatments the control group receive.

More formal psychological therapies are usually delivered by specialist psychological therapists through CBT based interventions and are delivered on a one-to-one basis. All standard treatment sessions have a duration range of 30–60 min and take place once or twice a week for a period of approximately 4–12 weeks. The number of interventions each participant will receive may vary. During treatment concomitant alcohol and drug/s use may be permitted, as well as any prescribed medication (detoxification included).

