Study groups will then complete a period of 4-weeks of substance misuse treatment, of either i) BFO plus standard treatment, or ii) standard treatment only. For the BFO group, the 4-week intervention will be delivered to groups of approximately 10 participants at a time, so it is estimated that approximately 6–8 groups will need to run successively to achieve the sample size required, in order to account for some attrition between baseline and 4-week post-treatment assessments. BFO group participants will receive two sessions of BFO each week, alongside any standard treatment they may be engaging with.

Online access to the BFO program is granted via the activation of an access code given to the participant at the alcohol and drug misuse service by authorized practitioners. To activate the access card and create a personal account, the participant must enter a username and password of his choice along with the access code. The practitioners will be able to assist with the online access if required. The participants must also agree to the Terms & Conditions of using BFO, which are in accordance with the Participant Information Sheet and Informed Consent Form and conform to the European Union General Data Protection Regulation around the use of digitally captured personal data. The practitioners must ensure that they log out of BFO at the end of each treatment session to protect the confidentiality of the data.

Procedures to enhance retention of participants during the 4-week treatment period will include practitioners providing ongoing support during weekly key-working sessions, which all offenders in the prison will routinely receive during the standard substance misuse treatment. When participants do dropout of the study, new participants will be recruited and randomized to replace dropouts, in order to ensure the required sample size of 120 participants (60 per group) complete the 4-week treatment period and provide post-treatment data. However, in line with ITT principles, all randomized participants, including dropouts, will be included in the final analyses (see ‘Data Analysis’ section). After completion of the 4-week treatment period, participants in both groups will complete the same battery of digital psychometric assessments on the prison desktop computers.

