### Data analysis

Quantitative data will be analyzed and reported using SPSS® Version 25.0 (or later) with all analyses to be performed as per the statistical analysis plan. The appropriate 95% - confidence interval will be applied. The *all-randomized population* will consist of all participants in the study that have been screened and allocated to either the i) BFO plus standard treatment, or, ii) standard treatment only group. The *per-protocol population* will consist of all participants randomized into the study who have completed the 4-week treatment period as well as all follow-up assessments.

Analyses will be performed on the basis of an ITT population, with the all-randomized population included in the analyses. No participants will be excluded from the ITT analyses, i.e. those who have withdrawn, been lost to follow-up, or have provided incomplete outcomes data. Separate analyses will also be conducted on the per-protocol population who have provided at least one set of follow-up data. Outcomes from these two analyses (ITT, per-protocol population) will be compared to examine whether missing data may have had an impact on reliability of conclusions formed around comparative effectiveness of the two study conditions.

Previous analyses (e.g. Elison et al. 2015a, b, c) indicate that data will likely be non-normally distributed in which case nonparametric repeated-measures analyses of covariance (ANCOVA) using appropriate distribution such as Poisson distribution, will be used to compare the study groups at 4-weeks post-treatment and 3- and 6-months follow-up on self-reported substance use, substance dependence, mental health sequelae, biopsychosocial functioning and quality of life. However, normality will be tested when data are available for analyses, and appropriate distributions will be applied.

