### Power calculation

Since the study is a parallel-group comparison, equal numbers of participants will be required for each of the groups; i) BFO plus standard treatment, and, ii) standard treatment only. The study projection of the sample size will require 60 evaluable participants in each treatment group to achieve enough power (assuming power of 0.80 with α = .05) with an allowance of 50% attrition at 3- and 6-months follow-up, which is in line with previous studies with offender populations receiving interventions for substance misuse in correctional settings (e.g. Crisanti et al. 2014). In addition, this level of attrition is also seen in substance misuse intervention research more generally (e.g. Brorson et al. 2013) and in many digital interventions studies (e.g. Eysenbach 2005). To obtain a total of 120 evaluable participants, it is estimated 240 participants will need to be recruited and screened.

These estimations have been based on previous samples used for assessments of CAT (Carroll et al. 2008), some of which have used longitudinal statistical analyses (Koski-Jännes et al. 2009; Kypri et al. 2008). It is envisaged that the estimated evaluable participant population will be sufficiently large to enable meaningful descriptive comparisons to be performed.

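### Delivery in arm-specific groups of about 10 is allowed for neither in the sample size nor in the ANCOVA as named, so stated power is too high and the test anti-conservative for any positive within-group correlation

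*Protocol article*

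**What the plan says.** Under Procedure, randomization is of individual men. BFO is then given in groups: "the 4-week intervention will be delivered to groups of approximately 10 participants at a time", with roughly 6–8 groups run one after another to reach the required size.

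Under Standard treatment, the low-intensity psychosocial component is delivered in "groups of participants that are of a similar size to the group sessions of BFO, i.e. groups of 10 participants". The arms are kept apart: "participants in the BFO group will receive their group-based standard treatment in groups that are run separately" from those of the control arm. The reason given is the stable unit treatment value assumption. Formal psychological therapy is one-to-one, and standard treatment is expected to vary between men.

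Data analysis names "nonparametric repeated-measures analyses of covariance (ANCOVA) using appropriate distribution such as Poisson distribution", with baseline scores controlled for. No group or practitioner term appears.

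Power calculation says the study "will require 60 evaluable participants in each treatment group" ("assuming power of 0.80 with α = .05"), with an allowance of 50% attrition that leads to 240 men recruited and screened. It states no effect size, ICC or design effect.

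**The concern.** Men who attend the same sessions with the same peers tend to have more similar outcomes than men in different groups. Where groups belong to one arm only, that shared variation adds to the variance of the treatment comparison. Individual randomization does not remove it, because the correlation arises after allocation, through delivery.

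Two things follow if it is ignored. A model without a group term gives standard errors that are too small, so intervals are too narrow and a nominal 5% test rejects too often under the null. And 60 men per arm carry less information than 60 independent men, so power is below the figure claimed. The first error favours declaring BFO effective. The article deals with contact between the arms, both in separating the groups and in its limitations. It does not mention correlation within a group, which the separation leaves in place.

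**Working it through.** **Inputs from the article.** 60 evaluable per arm with equal allocation ("equal numbers of participants will be required for each of the groups"); α = 0.05; power 0.80; attrition 50%; group size m about 10; 6–8 BFO groups.

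**Inputs assumed.** A two-sided test (sidedness is not stated; Data analysis mentions a 95% confidence interval). ICC 0.01 / 0.05 / 0.10. A continuous outcome compared at one time point, normal approximation, as a stand-in for the repeated-measures model.

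**Step 1: the plan's own figures.** 120 / (1 − 0.5) = 240, which matches the stated number exactly. The attrition allowance therefore uses up all of the inflation and nothing is left for a design effect. The 60 per arm cannot be reproduced without an effect size. Solved backwards, with independent men:

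d = (1.960 + 0.842) × √(2/60) = 2.802 × 0.1826 = 0.51.

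**Step 2: design effect.** DE = 1 + (m − 1) × ICC. With m = 10 this is 1.09 / 1.45 / 1.90. If both arms are fully clustered, the variance of the difference is multiplied by DE. If only the BFO arm is clustered, it is multiplied by the average of DE and 1, that is 1 + 4.5 × ICC = 1.045 / 1.225 / 1.45. Call this multiplier V.

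**Step 3: consequences.** At d = 0.51, power of a correct analysis = Φ(2.802/√V − 1.960). Type I error of the analysis that ignores groups = 2 × [1 − Φ(1.960/√V)].

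| Clustering | ICC | V | Power | Type I error |
|---|---|---|---|---|
| None | 0 | 1.00 | 80% | 5.0% |
| BFO arm only | 0.01 | 1.045 | 78.2% | 5.5% |
| BFO arm only | 0.05 | 1.225 | 71.6% | 7.7% |
| BFO arm only | 0.10 | 1.45 | 64.3% | 10.4% |
| Both arms in full | 0.01 | 1.09 | 76.5% | 6.0% |
| Both arms in full | 0.05 | 1.45 | 64.3% | 10.4% |
| Both arms in full | 0.10 | 1.90 | 52.9% | 15.5% |

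**Step 4: sensitivity to group size.** If 8 groups yield 60 evaluable men, m = 60/8 = 7.5 and DE = 1 + 6.5 × ICC = 1.065 / 1.325 / 1.65. If each group of 10 completes treatment and half are then lost by 3 and 6 months, m is about 5 and DE = 1.04 / 1.20 / 1.40. Smaller groups weaken the effect of clustering.

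**Step 5: few groups.** The normal approximation is generous. With 6 groups in each arm, both clustered, and a t reference on 10 degrees of freedom, power at d = 0.51 is 67.7% / 55.6% / 45.1%.

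**The case against.** Four objections carry weight.

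1. **Not all group variation is specific to an arm.** A reader might infer that nothing cancels between arms. The article does not support that. Under Procedure, practitioners deliver both BFO and the standard treatments, so facilitators may be crossed with arm. Men enter both arms over the same period, so calendar effects are partly shared. What remains specific to an arm is the effect of peers and sessions.

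2. **Control-arm clustering is only partial.** A reader might infer that every man in both arms sits in a fixed group of 10. Standard treatment is heterogeneous, some of it is one-to-one, and no fixed control cohort is described. The figures for both arms are therefore an upper case, and those for the BFO arm alone a lower one.

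3. **The size is assumed.** Neither the ICC nor d is in the article. BFO is used through personal accounts, is tailored to each man and is delivered in standardized form, all of which argue for a low ICC. At 0.01 the loss is about 2 to 4 power points.

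4. **The statistical analysis plan is not shown.** A reader might infer that the trial has decided to treat men as independent. The article does not say so, and the plan could add a group effect. The criticism of the ANCOVA therefore applies to the model as the article names it. The criticism of the sample size does not depend on the plan, because the basis for 60 per arm is set out and contains no allowance. Nor can a later plan model a variable that was not collected. The standard-treatment data listed in the article are type, number of sessions, kind of practitioner and medication, without group identity. The appendix form itself is not shown, and BFO attendance lists will exist.

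These points narrow the claim and its size but leave its direction unchanged.

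**Conclusion.** The point stands in this form. BFO is delivered in about 6–8 arm-specific groups and part of standard treatment in arm-separate groups. The sample size makes no allowance for correlation within groups, and the named ANCOVA has no group term. For any positive ICC, true power is below 80% and the test as named is anti-conservative.

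The direction is firm; the size is conditional. At ICC 0.05 with groups of 10 and the implied d of 0.51, power lies between about 72% (BFO arm only) and 64% (both arms in full), and type I error between 7.7% and 10.4%. At ICC 0.01 the effect is small. It also shrinks where fewer than 10 per group are evaluable, whereas allowing for the few groups lowers power further.

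**What to change.** - Record each man's BFO group and any standard-treatment group, with an identifier, as treatment is delivered.
- In the primary model include a partially nested random effect: BFO group as the cluster in the BFO arm; standard-treatment group as the cluster in the control arm where there is one; men without a group as singletons. Defining the BFO group as the cluster gives each BFO man one cluster even if he also attends a standard-treatment group.
- Use a small-sample correction, such as Satterthwaite or Kenward-Roger degrees of freedom where the model allows it, because there are few groups.
- Restate the Power calculation with an explicit effect size and a range of ICCs, showing the resulting power at the planned size. Enrolment need not change.

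The cost is one extra recorded field, somewhat wider intervals and a lower stated power.
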